## Abstract

**Background:**

The human immunodeficiency virus (HIV) and acquired immune deficiency syndrome (AIDS) continue to be a major public health problem in Sub-Saharan Africa (SSA), particularly in Swaziland, which has the highest HIV prevalence in this region. A wide range of strategies and interventions have been used to promote behavior change, though almost all such interventions have involved mass media. Therefore, innovative behavior change strategies beyond mass media communication are urgently needed. Serious games have demonstrated effectiveness in advancing health in the developed world; however, no rigorous serious games interventions have been implemented in HIV prevention in SSA.

**Objective:**

We plan to test whether a serious game intervention delivered on mobile phones to increase HIV risk perception, increase intention to reduce sexual partnerships, and increase intention to know own and partners HIV status will be more effective compared with current prevention efforts.

**Methods:**

This is a two-arm randomized intervention trial. We will recruit 380 participants who meet the following eligibility criteria: 18-29 years of age, own a smartphone running an Android-based operating system, have the WhatsApp messaging app, live in Swaziland, and can adequately grant informed consent. Participants will be allocated into a smartphone interactive, educational story game, and a wait-list control group in a 1:1 allocation ratio. Subsequently, a self-administered Web-based questionnaire will be issued at baseline and after 4 weeks of exposure to the game. We hypothesize that the change in HIV risk perception between pre- and post-intervention assessment is greater in the intervention group compared with the change in the control group. Our primary hypothesis is based on the assumption that increased perceived risk of HIV provides cues to engage in protective behavior. Our primary outcome measure is HIV risk perceived mean change between pre- and post-intervention compared with the mean change in the wait-list control group at 4-weeks post-intervention. We will use standardized regression coefficients to calculate the effect of the intervention on our primary outcome with *P* values. We will conduct both intention to treat and as treated analysis.

**Results:**

This study is funded by Hayao Nakayama Foundation for Science & Technology and Culture; Grant number H26-A2-41. The research and development approval has been obtained from Kyoto University Graduate School and Faculty of Medicine Ethics Committee, Japan, and Swaziland’s Ministry of Health Ethics and Scientific committee. Results are expected in February 2017.

**Conclusions:**

This study will provide evidence on the efficiency of a mobile phone interactive game in increasing HIV risk perception in Swaziland. Our findings may also be generalizable to similar settings in SSA.

**Trial Registration:**

University Hospital Medical Information Network Clinical Trial Registry ID number (UMIN-CTR):UMIN000021781; URL:https://upload.umin.ac.jp/cgi-open-bin/ctr_e/ctr_view.cgi?recptno=R000025103 (Archived by WebCite at http://www.webcitation.org/6hOphB11a).

## Introduction

It is estimated that 35.3 million people are living with human immunodeficiency virus (HIV) globally [1]. Sub-Saharan African (SSA) is the most affected region and the disease burden varies considerably between countries. In Swaziland, a land-locked, lower-middle income country surrounded by South Africa and Mozambique, HIV prevalence is estimated to be 26% among men and women of 15-49 years [2]. The overall HIV prevalence among the reproductive age population (18-49) has remained unchanged between 2006 and 2011 at 31% [3,4]. A recent, longitudinal, cohort study between December 2010 and June 2011 has estimated the incidence of HIV at 1.7% in men and as high as 3.1% in women [5]. Unprotected heterosexual transmission accounts for 94% of all new infections in the country [6]. More specifically, multiple concurrent partnerships have been identified as key drivers of HIV infection in Swaziland [6]. A recent qualitative study found that social and structural factors played a role in creating an enabling environment for high-risk sexual partnerships, and these factors included social pressure and norms, a lack of social trust, poverty and a desire for material goods, and geographical separation of partners [7].

Other key drivers have been highlighted in the Extended National Multi-sectoral HIV/AIDS Framework for 2014–2018 (eNSF) as: low rates of HIV testing (only 40% of people aged 15-49 had tested for HIV 12 months preceding a household survey) [8]; early sexual debut; low levels of medical male circumcision; and low HIV risk perception [8,9].

HIV is the leading public health concern in Swaziland [4]. National efforts have emphasized the scale-up of a combination of prevention approaches including: HIV testing and counseling, social behavior change communication, medical male circumcision, and HIV care and antiretroviral services. Despite this cocktail of prevention approaches, risky behaviors remain high. For example, Bicego and colleagues [4] note that there is still a low/late uptake of HIV testing services by men, which is consistent with late entry into care and treatment. Furthermore, according to the Swaziland Demographic Health Survey of 2006/07 and the Multiple Indicator Survey of 2010, the overall prevalence of multiple sexual partners remained unchanged at approximately 11% between 2006 and 2010 (data recalculated) [9,10]. On another note, the eNSF 2014-2018 points out that the Swaziland Social and Behavior Change strategy developed in 2010 has had limited success in facilitating desired levels of behavior change most importantly influencing personal HIV risk perception that focus on translating HIV awareness into protective action [8]. Beliefs about personal risk of HIV infection are central to motivate people to engage in behaviors that reduce their risk of HIV infection [11]. The Swaziland HIV testing and counseling guidelines includes HIV risk assessments to enhance self-perception of risk [12]. Models such as the Protection Motivation Theory and the Health Belief Model offer insights into the significance of perceived risk in adopting protective behavior. To date, there has been limited randomized control trials aimed at influencing how people perceived their risk of HIV in Swaziland.

Furthermore, anecdotal information suggests that there is information fatigue from the target audience in receiving HIV prevention messages from the mass media because most prevention campaigns have been dominantly delivered through mass media. One strategy that can break this perceived fatigue is the use of target audiences’ mobile phones. In developing countries, decreasing costs and increasing mobile network coverage provide a wide range of opportunities for apps using mobile phones [13]. Although comprehensive up to date data for mobile phone usage in Swaziland is limited, mobile phone penetration is estimated at 87% [14]. Our consultative meeting with the only mobile carrier in Swaziland revealed that there are currently 206,880 smartphones on the mobile network (as of June 2015). Therefore, our study seeks to use serious games delivered via mobile smartphones to engage the target audience in creative ways to increase personalization of HIV risk.

In this study, we adopt the definition of Serious Games as proposed by Alvarez and Djaouti [15], “a computer application whose intended purpose is to coherently combine both serious aspects such as, but not limited to teaching, learning, communication, or information, with game playing aspects from video games.” These combined serious aspects and playing aspects form a utilitarian scenario, which in computer terms uses a sound and graphics package, a story and appropriate rules, and is therefore distinct from simple entertainment [15]. Alvarez and Djaouti [15] summarize this definition by the following relationship:

Utilitarian scenario + gaming scenario => Serious Games.

Current literature suggests that serious games are effective in changing behavior. For example, a randomized trial (in the United States) designed to improve treatment adherence among 13- to 29-year-old patients with malignancies including acute leukemia, lymphoma, and soft-tissue sarcoma found that among 200 participants who were prescribed oral trimethoprim-sulfamethoxazole and 6-mercaptopurine, 16% indicted an increase in adherence for the serious games intervention group compared with the control group. Mixed-effect linear model analyses of chemotherapy metabolite concentrations showed that patients in the intervention group maintained significantly higher chemotherapy metabolite levels over time than did patients in the control group (significant group × time interaction; *P*=.002)[16]. Additionally, another clinical trial conducted in the United States among 935 males who had sex with males between 18- and 24-years old aimed at reducing risky sexual behavior and sexual shame, found that exposure to a serious games intervention led to immediate shame reduction for those in the serious games intervention group compared with the control group (mean [M]=−0.08, standard deviation [SD]=0.51, n=437 compared with M=0.07, SD=0.54, n=484, respectively; the difference was statistically significant at *t*
_(919)_=4.24, *P*< .001) [17]. Despite the success of serious games in advancing health, no randomized intervention trials have been conducted in HIV prevention in SSA or in Swaziland. To address these research gaps, our goal is to design a serious game to increase HIV risk perception and use randomization to evaluate the efficacy of this intervention among 18- to 29-year-old people in Swaziland.

## Methods

### Study Design and Hypotheses

The Swaziland Serious Games–Based HIV Prevention Trial (SGprev trial) will be a 4-week, two-arm randomized intervention trial. Participants will be randomized into 2 groups (the intervention group and a wait-list control group) in a 1:1 allocation ratio (Figure 1) [18]. The intervention will be downloadable from our website, on the Google Play store, and in popular cellular shops around Swaziland. These cellular shops already serve as distribution sites for other mobile software and apps, such as antiviruses, Opera mini, and WhatsApp, and are thus very popular in Swaziland. Additionally, the game will also be available from kiosks in all tertiary institutions in the country. Downloading the game will not be synonymous with enrolling in the trial. After downloading the game, potential participants will be redirected or prompted to visit our website where information about the trial and eligibility screening will be provided.

We plan to test whether a serious game intervention delivered on mobile phones to increase HIV risk perception, increases the intention to reduce multiple sexual partnerships, intention to know own HIV status, and intention to know all sexual partners’ HIV status will be more effective compared with current prevention efforts. Therefore, our hypotheses are that

1. The change in HIV risk perception between pre- and post-intervention assessment is greater in the intervention group compared with the change in the control group.

2. The change in HIV risk perception between pre- and post-intervention assessment will be greater among those reporting high HIV risk behavior in the intervention group compared with the control group.

3. The change in intention to have an HIV test between pre- and post-intervention assessment will be greater in the intervention group compared with the change in the control group.

4. The change in intention to reduce multiple concurrent partnerships between pre- and post-intervention assessment will be greater in the intervention group compared with the change in the control group.

5. The intervention group will report higher rate of condom use in the last sexual encounter compared with the control group.

**Figure 1 figure1:**
[figure not shown]
CONSORT diagram for Swaziland serious games-based trial.

### Participants, Setting, and Intervention

Our target population is Swazi males and females between 18- to 29-years old currently in Swaziland. Our intervention study targets people between 18- and 29-years old for the following reasons: (1) according to Bicego and colleagues [4], young people between this age group are most vulnerable to HIV because of their low HIV-testing behavior, (2) our primary study recruitment platform will be Facebook because the majority of mobile phone users in Swaziland also use Facebook, and (3) in our formative research (unpublished work, 2014) we found that this age group is likely to use smartphones and be literate on navigating the Internet compared with younger than 18-years-old or older than 29-years-old participants. Moreover, this age group is likely to find the SwaziYolo game entertaining.

### Inclusion Criteria

For this study, we will include males and females if they meet the following criteria: (1) are between 18 and 29 years of age, (2) own a smartphone running an Android-based operating system, (3) currently have the WhatsApp messaging app, (4) currently live in Swaziland, and (5) are able to adequately grant informed consent.

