### Description of the Intervention

SwaziYolo (a smartphone game) is an interactive, educational story game that puts the player in the role of a young adult looking for love in Mbabane (the capital city of Swaziland), making important choices about relationships and sexual health (see Multimedia Appendix 1 for an overview of the steps taken in developing the intervention). The intervention is guided by cognitive-based approaches such as the Theory of Planned Behavior to target intentions to engage in HIV protective behavior [20-22] and the Health Belief Model to target perceived susceptibility of acquiring HIV infection [20]. While capitalizing on elements of serious games such as immersion, role-playing, and a dynamic storyline, the game exists in two major parts: the first is set in an imaginary social network called SwaziYolo, which is meant to resemble a combination of existing tools like Facebook, OKCupid, and Whatsapp. Here, players register (registration and login screen), view pictures (potential love interests “Connections” screen) and profiles of potential love interests (profile mode screen), and have Web-based chats (chat mode screen) with various characters. The other half of the game takes place in various made-up locations around Mbabane, such as nightclubs and cafes (meet up at a club screen) where players regularly go on dates referred to in the game as “meet-ups.” In both parts of the game, players are regularly required to choose between several courses of action to progress a conversation or storyline with a friend or love interest (chat mode screen). The decisions they make will influence the opinions and behavior of other characters, as well as the player’s own health and safety. Eventually, feedback is given based on choices made (feedback from a medical doctor at a clinic screen). In the game, the various character dialogues and scenes, will address the issues identified in our formative research such as HIV risk perception, raising knowledge of their own HIV status as well as a sexual partner’s HIV status, reducing multiple concurrent sexual partnerships, and consistent condom use.

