### Measurement Instrument

A self-administered structured Web-based questionnaire was created based on review of both Swazi and international literature. For example, questions relating to sociodemographic characteristics were adopted from the 2007 Swaziland Demographic Health Survey, and those related to risky sexual behavior and intention to change behavior were developed from our formative studies. Additionally, the Perceived Risk of HIV Infection Scale (PRHS; found to have excellent internal consistency Cronbach alpha=0.88) [11] will be used to assess the primary outcome of this study. Past research has used a variety of approaches to measure HIV risk perception including single likelihood assessments [21,25]. The 8-item PRHS scale incorporates items assessing cognitive assessments of risk (eg, chance of infection), as well as intuitive assessments (eg, feeling vulnerable, worry, gut feeling about likelihood), and salience of risk (eg, thought about risk, can picture it happening) to provide a more comprehensive measure of perceived risk of HIV infection, thus our choice to use this scale. The questionnaire will be converted into a Web-based format accessible via a link. Detailed variables assessed by the questionnaire are described in the section below and the questionnaire is presented in Multimedia Appendix 2. The trial tools were piloted among respondents known to the principal investigator, who will not be part of the main trial, in order to assess Web-based eligibility screening functionality; user verification; participant randomization functionality; questionnaire skip logic functionality; and the average length of time it takes to complete the questionnaire.

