#### Secondary Outcomes Measure

The secondary outcomes for this intervention are self-reported intention to have an HIV test; intention to reduce multiple concurrent sexual partnerships; and an increase in reported condom use in the last sexual encounter (Table 1).

**Table 1 table1:** Secondary outcome measures.

Measures		Baseline	Follow-up at 4 weeks

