**Demographics**			
	Age	X	
	Level of education	X	
	Employment status	X	
	Income level	X	
	Marital status	X	
	Ever tested for HIV	X	X

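### Eligibility admits people who already know they are HIV-positive, for whom perceived risk of infection (the primary outcome) and intention to test have no valid answer

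*Protocol article*

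**What the plan says.** The Inclusion Criteria section gives five conditions, the last two being "4) currently live in Swaziland, and (5) are able to adequately grant informed consent". The Methods paragraph of the abstract repeats the set, ending "live in Swaziland, and can adequately grant informed consent". Neither place mentions HIV status, and the article gives no exclusion criteria.

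The Introduction makes HIV-positive applicants foreseeable. It says that "HIV prevalence is estimated to be 26% among men and women of 15-49 years", and that the figure for ages 18-49 "has remained unchanged between 2006 and 2011 at 31" percent.

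The primary outcome is the change in PRHS score over 4 weeks. Measurement Instrument says the scale was chosen "to provide a more comprehensive measure of perceived risk of HIV infection", with items on chance of infection, vulnerability and worry. Description of the Intervention says the game uses the "Health Belief Model to target perceived susceptibility of acquiring HIV infection". The secondary outcomes include "self-reported intention to have an HIV test", which is also hypothesis 3.

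Table 1 lists "Ever tested for HIV", and the partner's testing and status, but not the participant's own result. The primary analysis neither restricts nor stratifies by HIV status.

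**The concern.** A person with a known HIV diagnosis has no chance of becoming infected to rate and no first diagnosis to seek. Whatever score that person gives, high, low or blank, does not measure susceptibility. The primary estimate would then average over some people for whom the question is undefined, and so would the result for hypothesis 3.

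The planned subgroup is exposed too. Under Secondary Outcome Measures in the analysis section, participants with low risk perception and no condom use at last sex are to be analysed as the group most at risk. A known-positive participant with a low PRHS score and no condom use would be counted there as someone who underestimates personal risk. That misreads the score.

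There may also be a cost in precision. Participants who cannot respond on the outcome pull the mean difference towards zero. If the questionnaire routes them past the items, they become missing primary outcomes after randomisation.

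**Working it through.** **Inputs.** From Sample Size Calculation: difference δ = 0.477, SD σ = 1.03, two-sided α = 0.05, power 0.80, 1:1 allocation, 30% loss, final N = 380 with 190 per gender. The known-positive share p at ages 18-29 is not in the document. I assume 5% to 26%. The top value would require the prevalence quoted for ages 15-49 to apply at 18-29 and every infected person to be diagnosed.

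**The plan's own figure.** n per arm = 2 × (1.960 + 0.842)² × 1.03² / 0.477² = 73.2, against the stated 73 (146 in total). This reproduces when 0.477 is read as a difference on the score scale, which is 0.477 / 1.03 = 0.463 SD. Then 146 × 1.30 ≈ 190 and 190 × 2 = 380. No sample-size figure is disputed here.

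**Completers.** 380 × 0.70 = 266, or 133 per arm and 66.5 per arm within one gender. Power by the two-sample t test with p = 0 is 96.4% overall and 75.5% within one gender.

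**Dilution.** If known-positive participants show no effect, the expected difference is δ(1 − p): 0.477 × 0.95 = 0.453 at 5%, and 0.477 × 0.74 = 0.353 at 26%. Two assumptions about their variance bracket the result, taking 1.03 as the SD of the change score.

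- *Full variance:* their change scores vary as much as anyone's, so the SD stays at 1.03. The standard error is 1.03 × √(2/133) = 0.126.
- *Zero change:* they sit at the same score at both visits. The variance is (1 − p)σ² in the control arm and (1 − p)σ² + p(1 − p)δ² in the intervention arm. At p = 0.26 these are 0.785 and 0.829, so the standard error is √((0.785 + 0.829)/133) = 0.110.

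| p | Affected of 380 | Difference | Overall, full variance | Overall, zero change | One gender, full variance | One gender, zero change |
|---|---|---|---|---|---|---|
| 0 | 0 | 0.477 | 96.4% | 96.4% | 75.5% | 75.5% |
| 5% | 19 | 0.453 | 94.7% | 95.5% | 71.2% | 73.1% |
| 10% | 38 | 0.429 | 92.3% | 94.4% | 66.5% | 70.6% |
| 15% | 57 | 0.405 | 89.2% | 93.1% | 61.5% | 67.9% |
| 20% | 76 | 0.382 | 85.3% | 91.5% | 56.4% | 65.0% |
| 26% | 99 | 0.353 | 79.5% | 89.1% | 50.1% | 61.4% |

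Overall power stays at about 80% or more throughout. The one-gender figure is already below 80% with no known-positive participants, so most of that shortfall at small p has another source.

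**Order of steps.** Baseline Data Collection places eligibility screening and consent first, then randomisation, then the baseline questionnaire. The Randomization section says participants are not blinded. A status item in the baseline questionnaire would therefore be answered after allocation.

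**The case against.** Four points on the other side have weight.

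- *The prevalence is not the affected share.* A reader might infer that 26% to 31% of participants are affected. The document does not support this. Those figures cover ages 15-49 and 18-49 and include undiagnosed people, who can answer the scale validly. The Introduction reports that only 40% had tested in the previous 12 months, and the 18-29 group was chosen partly for its low testing. The known-positive share is probably well below 26%. This stands.
- *Status may be collected.* A reader might infer from Table 1 that own status is never asked. Table 1 covers secondary measures and also omits the PRHS and gender, both of which are certainly collected. The questionnaire is in an appendix that is not shown, and it uses skip logic. So non-collection is not established. Eligibility would be unchanged either way, and routing such participants past the items would only turn invalid scores into missing ones.
- *No bias between arms.* Randomisation balances known-positive participants on average. The expected error is towards the null. This stands.
- *Broad enrolment can be defended.* The stated target is all Swazi 18-29-year-olds, and condom-use and partner outcomes remain meaningful for HIV-positive people. Asking for status on a website reached from an advertisement invites some misreporting. This supports keeping these participants for the other outcomes. It does not make the PRHS or intention to test valid for them.

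That known-positive participants would score at the floor or ceiling is also an assumption, which is why two variance cases are shown.

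**Conclusion.** The point holds as a matter of validity. As written, the criteria admit people for whom the primary outcome and hypothesis 3 are undefined, and nothing in the article sets them aside. The low-risk-perception subgroup inherits the same problem.

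The loss of power is secondary. It rests on an assumed share of 5% to 26%, on 30% loss, on 1.03 as the SD of change and on no effect in those affected. It would be wrong to present this as a trial that loses its power or is biased between arms: overall power stays between 95.5% and about 80% under either variance assumption. The change is worth making before recruitment because the article describes the trial as not yet started and the remedy is small.

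**What to change.** Add one confidential, optional self-report item on known HIV-positive status to the existing web eligibility screening, ahead of randomisation. Then choose one of two rules and state it in the protocol:

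1. Exclude those who report known positive status. Recruitment already runs until the target is met. For shares of 5% to 26%, 380/0.95 = 400 to 380/0.74 = 514 otherwise eligible applicants would be needed.
2. Enrol them, but prespecify that the PRHS and intention-to-test analyses, and the low-risk-perception subgroup, cover participants who did not report known positive status at screening. Keep everyone for the condom-use and partner outcomes. If 380 is not raised, 133 × 0.95 = 126 to 133 × 0.74 = 98 completers per arm remain for the PRHS, with overall power of about 96% to 90%.

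Under either rule, treat a blank answer as not reporting known positive status. Do not define the population from the baseline questionnaire unless that questionnaire is moved ahead of randomisation.

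The cost is one sensitive question, an ethics amendment and slightly slower recruitment. Some misreporting will remain. Because it occurs before allocation, it should fall equally on both arms on average.
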